##### Implementation outcomes

Participants will be asked to complete measures evaluating the implementation outcomes of the ISMM. The first three surveys evaluating feasibility, acceptability, and appropriateness are comprised of 4 items, utilizing a 4-point Likert scale (1—“completely disagree” to 4— “completely agree”). These measures have robust psychometric properties, including discriminant content validity and test–retest reliability, and have been utilized across contexts [32]. The last survey is comprised of 10 items and uses a 5-point scale (strongly disagree to strongly agree; [33]).

**Feasibility of Intervention (FIM)**

The FIM will examine participant perspectives on “the extent to which a new… innovation, can be successfully used or carried out within a given agency or setting” (e.g., “[ISMM] seems easy to use”).

**Acceptability of Intervention Measure (AIM)**

The AIM will measure “the perception among implementation stakeholders that a given treatment, service, practice, or innovation is agreeable, palatable, or satisfactory” (e.g., “[ISMM] meets my approval”).

**Intervention Appropriateness Measure (IAM)**

The IAM will examine “perceived fit, relevance, or compatibility of the innovation for a given practice setting, provider, or consumer; and/or perceived fit of the innovation to address a particular issue or problem” (e.g., “[ISMM] seems fitting”).

**Implementation Strategy Usability Scale (ISUS)**

The ISUS will examine the perceived usability—“the extent to which an intervention can be used by specified users to achieve specified goals with effectiveness, efficiency, and satisfaction” of the concept mapping method. (e.g., “I think I would like to use [ISMM] frequently”).

#### Qualitative interview

##### Semi-structured individual interviews

The interview protocol will be developed following quantitative data collection and analysis. The interview will further explore staff perspectives on the impact of the ISMM on the organization’s readiness to change, implementation outcomes related to the ISMM, and suggestions to improve the ISMM. Interview questions will be developed to align with constructs from the CFIR. Participants will be asked about perspectives on intervention (i.e., ISMM) characteristics, outer and inner settings factors, and individual (i.e., staff) characteristics that influenced the perceived feasibility, acceptability, and appropriateness of the ISMM as well as how these factors influenced perceived organizational readiness for change.

#### Processes

Aim 1 findings will inform the selection of one ISMM that is identified as (1) being evidence-based and feasible for use and (2) an approach that includes stakeholder engagement in the process.

Regardless of the ISMM selected after completing the scoping review, measures and data analysis will remain the same. Additionally, initial research procedures are similar across ISMMs, and steps to map implementation strategies will be adjusted according to the ISMM selected. All ISMM methods begin with a process for identifying implementation barriers and facilitators. Aim 2 of this study will utilize a strength and needs’ assessment to identify and prioritize implementation barriers and facilitators to implementing Project ImPACT within each agency. Next, participants at each agency will be guided to use the Expert Recommendations for Implementing Change (ERIC; [7]) list of implementation strategies. Participants will use the ERIC to select implementation strategies they believe will address identified determinants (e.g., “access new funding” to address limited funding). They will also be provided the opportunity to generate any additional implementation strategies they believe may be relevant. Next, participants will sort and rank strategies in order to prioritize implementation strategies that may be most feasible and useful for their setting, as well as tailor strategies as needed. Procedures to tailor or adapt strategies will depend on the ISMM selected.

#### Analyses plan

##### Quantitative analysis plan

The quantitative data collected from questionnaires will be analyzed in three phases. First, analyses will focus on detecting and correcting potential data errors, describing properties, and evaluating the quality of the data. Descriptive analyses will be completed (i.e., means, frequencies, distributions) to report demographic data. Given the limited sample size, paired sample *t*-tests will be conducted to test for changes in perceptions as reported on the ORCA, ORIC, and ORC between pre-and post-ISMM at each agency. Finally, mean responses to the AIM, IAM, FIM, and ISUS will be aggregated by agency after completing the ISMM process to examine the implementation outcomes associated with the ISMM.

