The current study aims to (a) identify methods that may be used to select and tailor implementation strategies to unique contexts, and (b) evaluate implementation outcomes and organizational impact of one implementation strategy mapping method (ISMM) within the context of CMH agencies. Specifically, this project will focus on implementation efforts within CMH agencies in Michigan that are interested in utilizing Project ImPACT with their autistic clients enrolled in Medicaid benefits. Exploring methods to systematically tailor the implementation process and increase utilization of Project ImPACT within CMH agencies may support increased service equity and ultimately improve patient outcomes for autistic children experiencing socioeconomic disadvantage. The work in the funded project will proceed in two phases with two corresponding specific aims:*Aim 1:* Conduct a scoping review of implementation strategy mapping methods (ISMMs), or methods to select, tailor, and map implementation strategies, to address unique determinants within the context of child mental health service delivery settings.*Aim 2:* Pilot test the use of one ISMM within Michigan CMH agencies providing services to autistic youth whose services are funded by the Medicaid Autism Benefit. Specifically, aim 2 will examine whether the ISMM increases organizational readiness to change from pre- to post-ISMM, and will evaluate implementation outcomes (i.e., perceived feasibility, acceptability, and appropriateness; usability) of the ISMM for selecting and tailoring implementation strategies.

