### Aim 2: pilot test the use of one ISMM within Michigan CMH agencies providing services to autistic youth whose services are funded by the Michigan Medicaid Autism Benefit

Specifically, aim two will examine whether the ISMM increases organizational readiness to change from pre- to post-ISMM, and will evaluate implementation outcomes of the ISMM for selecting and tailoring implementation strategies, including perceived feasibility, acceptability, appropriateness, and usability.

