#### Setting

Purposeful sampling will be utilized to recruit five community-mental health (CMH) agencies in Michigan. Agencies interested in participating will attend a recruitment meeting with the Principal Investigator to review study details and benefits. Agencies will be eligible if they (a) provide services to children on the autism spectrum who are enrolled in Medicaid benefits, (b) identify a need for implementing Project ImPACT within their agency, and (c) endorse an interest in utilizing systematic implementation strategies to facilitate this process.

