#### Participants

We will recruit five directors/agency leaders, supervisors, and direct providers at each of the eligible agencies (expected *N* = 25). Participants will be recruited during the agency recruitment meeting and will be asked to complete an online screening form to determine eligibility, if they are interested in participating. Directors/agency leaders will be eligible if they fulfill the role of director or leading decision-maker regarding interventions provided within their agency. At least 1 director/agency leader will be required to participate. Supervisors and direct providers will be eligible if they provide or oversee staff who provide interventions to autistic children who receive their services via the Michigan Medicaid Autism Benefit. Agency staff will be ineligible if they do not read or speak in English.

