##### Readiness for change

Three measures will be utilized to measure readiness for change prior to, and upon completion of, the ISMM. The Organization Readiness for Implementing Change (ORIC; [29]), Organizational Readiness for Change Assessment (ORCA) context scale [30], and Organizational Readiness for Change (ORC; [31]) will be used to elicit participant perspectives regarding their organization’s motivation and capacity to support and facilitate the use of new interventions, such as Project ImPACT, within their organization.

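### Readiness change is tested separately in each agency on about five pairs, with no overall estimate, although Aim 2 asks about the mapping method as a whole

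*Protocol article*

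**What the plan says.** Aim 2 is introduced in the Background of the Protocol article with the statement that "aim 2 will examine whether the ISMM increases organizational readiness to change from pre- to post-ISMM". It also sets a second task, which is to evaluate feasibility, acceptability, appropriateness and usability. The heading section for Aim 2 repeats both. The readiness question is put for the method, not agency by agency.

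On sample size, Setting says "Purposeful sampling will be utilized to recruit five community-mental health (CMH) agencies in Michigan", and Participants says "We will recruit five directors/agency leaders, supervisors, and direct providers at each of the eligible agencies", with 25 expected in all. On measures, Readiness for change says "Three measures will be utilized to measure readiness for change prior to, and upon completion of, the ISMM". These are the ORIC, the ORCA context scale and the ORC, and none is named as primary.

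The Quantitative analysis plan opens its statement of the test with "Given the limited sample size, paired sample" t-tests, and says that these "will be conducted to test for changes in perceptions as reported on the ORCA, ORIC, and ORC between pre-and post-ISMM at each agency". The sentence after it aggregates the implementation outcomes by agency. No section describes an analysis of readiness across agencies or a rule for combining the five agency results. The Processes section of Aim 2 adds that the analysis stays the same whichever mapping method is chosen.

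**The concern.** The question concerns one method used in five agencies, while the tests concern five agencies one at a time. The reason given for the test, a small sample, is a reason not to divide 25 people into five groups of five.

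Followed as written, the plan yields up to 15 p-values from very small samples. Most would be non-significant even if readiness truly rose, and some could be significant by chance. Neither pattern answers the readiness question. The pilot would also end without an overall mean change and confidence interval to carry into a later study.

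**Working it through.** **Inputs from the Protocol article.** Five agencies (Setting), five staff per agency (Participants), three readiness measures (Readiness for change), and a paired t-test at each agency (Quantitative analysis plan). The stated total is reproduced: 5 × 5 = 25.

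**Assumptions, because the article gives no figure.** Two-sided 5% level. Mean change d of 0.3 to 1.0 SD of the change score. Intra-agency correlation (ICC) of change scores from 0 to 0.3.

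**1. The planned tests.** With n pairs, power follows the noncentral t distribution with n − 1 df and noncentrality d√n. For n = 5 the critical value is 2.776 on 4 df.

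| True change d | Noncentrality d√5 | Power |
|---|---|---|
| 0.3 | 0.67 | 8% |
| 0.5 | 1.12 | 14% |
| 0.8 | 1.79 | 28% |
| 1.0 | 2.24 | 40% |

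- 80% power requires d = 1.68.
- The 95% confidence interval has half-width 2.776/√5 = 1.24 SD.
- A one-sided 5% test gives 24% at 0.5 SD and 44% at 0.8 SD, so sidedness does not change the picture.

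**2. The set of tests.** There are 5 × 3 = 15. If nothing changes, the chance of at least one significant result is up to 1 − 0.95^15 = 54%, taking the tests as independent. The three scales come from the same staff, so the true figure is probably lower. If the true change is 0.8 SD in every agency, the chance that three or more of the five reach significance on a given measure is 14%. At 0.5 SD it is 2%.

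**3. Overall mean change, for these five agencies.** Regress each person's change score on agency and average the five agency means with equal weights. Residual df are 25 − 5 = 20, the critical value is 2.086, and the noncentrality is 5d, with d in within-agency SDs. Power is 30%, 66% and 97% at 0.3, 0.5 and 0.8 SD. 80% power requires 0.59 SD, and the half-width is 2.086/5 = 0.42 SD.

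**4. Overall mean change, for agencies beyond these five.** Apply a one-sample t-test to the five agency mean changes, with 4 df and noncentrality 5d/√(1 + 4·ICC).

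| ICC of change | Power at 0.5 SD | Power at 0.8 SD | d for 80% power |
|---|---|---|---|
| 0 | 48% | 84% | 0.75 |
| 0.1 | 37% | 72% | 0.89 |
| 0.2 | 30% | 61% | 1.01 |
| 0.3 | 26% | 53% | 1.12 |

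**5. Why the two must be kept apart.** If the test in step 3 is used to speak about other agencies, its standard error is too small by the factor √[(1 + 4·ICC)/(1 − ICC)]. At ICC 0.2 this is √(1.8/0.8) = 1.5, so the effective critical value is 2.086/1.5 = 1.39, which on 20 df is a true error rate of 18%. The rate is about 11% at ICC 0.1 and 25% at ICC 0.3, in agreement with simulation. A plain paired t-test on all 25 that ignores agency has about 10%, 14% and 19% at the same three values.

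**6. Where agency must enter.** Write each score as agency level + person level + time effect + error. An agency main effect and a participant intercept both cancel from post minus pre. With complete pairs, a model holding only these terms and time gives the same estimate and standard error as the paired t-test on all 25. The 20 df of step 3 require agency effects on the change itself, which is the same as an agency-by-time term.

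**The case against.** Aim 2 is a pilot, and low power alone is not an error in a pilot. Readiness is one of two stated questions, and Considerations and limitations puts acceptability, feasibility, appropriateness and usability first. Agency-level results also have a use: the mapping is done within each agency, Design evaluates implementation outcomes for each organization, and the joint display in the integration section explores quantitative data at each organization. All of this stands. It supports describing each agency. It does not support up to 15 significance tests in place of an overall estimate.

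The phrase about each agency might be read as saying only where change is measured. That is possible but weaker, since no pooled analysis appears anywhere and the next sentence also aggregates by agency.

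The pooled estimate has limits of its own. Its 66% is the favourable case, power at 0.5 SD stays below 80% in both overall analyses, and five agencies say little about how much agencies differ.

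A reader might also infer that the plan mishandles staff who lack a post score. The article does not set out missing-data handling, which a condensed article commonly leaves to the full protocol, so that is not part of this point.

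**Conclusion.** The point holds as a mismatch between question and analysis. One Aim 2 question concerns the method overall, and the plan tests it only agency by agency on about five pairs, with no overall estimate. At a true change of 0.5 SD, power is 14% per agency test, against about 66% for the overall change in these five agencies and 48% to 26% for inference beyond them. The sample and measure counts come from the article. The level, effect sizes and ICC are assumptions, shown as ranges.

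Two stronger conclusions are tempting and are not supported. One is that Aim 2's main question cannot be answered: readiness shares Aim 2 with the implementation outcomes, and what is lacking is an overall summary, not the data. The other is that pooling settles the matter without cost: the result is either confined to these five agencies or rests on 4 df, three measures remain with none primary (up to 1 − 0.95³ = 14% family-wise error), and the pre-post design has no control. The change should be made, but the study does not fail without it.

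**What to change.** Replace the agency-level tests in the Quantitative analysis plan with the following, for each readiness measure:

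- Report one overall mean change with a 95% confidence interval, from all participants' change scores regressed on agency with equal weights (20 df). If it is written as a repeated-measures model, include the agency-by-time term. State that the estimate applies to these five agencies.
- Alongside it, report the t-test and interval from the five agency mean changes (4 df) as the analysis for any statement beyond these agencies.
- Show agency-specific changes descriptively, without p-values, for the joint display.

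Naming one readiness measure as primary would deal with the remaining multiplicity.

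The cost is analysis wording only, with no new data or participants. Agency-level p-values are given up, and they carry little information at five pairs. The fixed-agency result must not be generalised, and the absence of a control remains a limitation to state.

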##### Qualitative analysis plan

Interview data will first be transcribed and verified by the research team. We will utilize thematic analysis [34] to analyze the qualitative interviews. Two independent coders will collaboratively develop a coding schema to explore concepts related to ISMM implementation outcomes, impact on organizational readiness for change, and overall perspectives regarding the ISMM, in alignment with CFIR constructs across all 5 domains. Emergent codes will also be identified when relevant. Next, the frequency and saliency of each code will be determined, and codes will be grouped into broader categories. The final step will be to identify overarching themes that summarize the qualitative data. Consensus coding procedures will be utilized throughout the process to address coding discrepancies. All data will be analyzed with MAXQDA software. We will adhere to the Standards for Reporting Qualitative Research [35] in order to ensure transparency and accuracy throughout qualitative data collection, analyses, and reporting.

##### Integration of QUAN and QUAL data strands

Qualitative data will be quantized to examine the frequency of each code across interview transcripts and to facilitate assessment of the saliency of each code. Both the quantitative and qualitative data strands will be analyzed independently first. Next, data strands will be merged in a joint display (i.e., side by side comparison table; [36]) in order to integrate findings from both quantitative and qualitative data, to understand where participant’s perspectives may converge or diverge, and to contextualize the quantitative findings. For example, quantitative data on the average acceptability of the ISMM will be explored at each organization and then further explored through utilization of the qualitative findings, when contrasting and comparing these findings in the joint display. Overall, merging the quantitative and qualitative data strands will allow for a deeper understanding of the specific components that participants found acceptable, factors influencing their perspectives on acceptability, and barriers and facilitators to acceptability.

## Discussion

### Innovation and impact

Overall, the current project, which includes a scoping review and pre-implementation study, aims to advance our knowledge of effective methods for selecting, tailoring, and mapping implementation strategies to context-specific implementation determinants. Specifically, this project will provide the first scoping review of methods to select, tailor, and map implementation strategies to address unique determinants within a given setting (Aim 1). Given the large number of discrete implementation strategies, these findings will advance our knowledge of how to select strategies that best fit an organization and inform future tailored EBP implementation efforts. Secondly, this project will be the first to evaluate the use of an ISMM within CMH agencies that provide services to autistic children experiencing socioeconomic disadvantage. The pre-implementation study (Aim 2) will substantially advance our knowledge of effective strategies for selecting, tailoring, and mapping implementation strategies to combat barriers and leverage facilitators that are unique to Michigan CMH agencies. Findings will support future ASD-EBP implementation efforts within low-resourced communities, with the ultimate goal of increasing equity in access to EBPs for this population. Finally, this project will contribute to growing science found at the intersection of implementation science and autism research by utilizing an implementation determinants framework, the CFIR, to evaluate the use of an ISMM within the context of CMH agencies providing services to autistic youth from low-resourced communities. While this framework has been previously utilized or is currently being tested in studies exploring implementation strategy mapping, it has not yet been used to explicitly guide data collection and analysis. Therefore, this study will utilize a mixed-methods research design to incorporate the CFIR as a guiding framework to understand stakeholder perspectives related to the use of the ISMM within CMH agencies providing services to autistic youth.

### Considerations and limitations

While this innovative line of study has potential for ultimately increasing equitable access to ASD-EBPs for autistic youth and their families through improved implementation processes, specific project limitations exist and must be considered. The scoping review (Aim 1) may not yield only one feasible and effective ISMM (e.g., equivocal outcomes may be found for 2 or more ISMMs). Studies of ISMMs are nascent; thus, there may be a paucity of existing literature evaluating ISMM strategies. Further, article eligibility/ineligibility criteria may reduce the number of articles included in the scoping review. If the scoping review does not yield one obvious ISMM to utilize in Aim 2, study personnel will discuss advantages and disadvantages of the identified ISMMs, consult with implementation science and community engagement experts, and determine one specific ISMM to be utilized in the pre-implementation study.

Additionally, because the goal of Aim 2 is to conduct foundational pilot research on the acceptability, feasibility, appropriateness, and usability of an ISMM, other implementation outcomes, such as adoption, fidelity, costs, and sustainability, will not be evaluated. While important constructs within implementation science, recent guidance suggests the need to conduct feasibility and pilot studies on implementation strategies, such as ISMMs, in order to identify potential revisions to the strategy, refine the research design and procedures for future implementation studies, or test the preliminary effects of the strategy on relevant implementation, service and individual-level outcomes [37, 38]. As stated by Proctor and colleagues [5], “the study of implementation strategies should be approached in a similar fashion as evidence-based interventions, for strategies are in fact a type of intervention” (p. 3). Thus, implementation strategies, in their own right, should be empirically tested prior to broader use to ensure that only evidence-based implementation strategies are being disseminated and utilized in usual care settings [4]. Further, this study will include a small number of CMH agencies in Aim 2 study procedures. As a result, the results of the pilot study may not be generalizable to broader systems, geographical locations, or populations. However, the goals of Aim 2 are to gather feasibility data-related implementation strategy procedures and study methods as well as assess potential implementation strategy effects to the use of ISMM within this common service system for autistic youth (e.g., prioritizing external validity) [5, 37, 39].

